# **ETHICAL CONSIDERATIONS**

## **5.1. Approval by the Ethics Committee of Federal University of Pelotas**

This research project will be submitted for evaluation by the Federal University of Pelotas Research Ethics Committee (REC), via Plataforma Brasil, and will only begin after approval. The study will be conducted in accordance with the standards of “Good Clinical Practice”. All research participants will sign a consent form (Appendix A).

It should be noted that the product to be tested already has a similar formulation in different products sold on the Brazilian market. In this sense, it is important to point out that none of the products to be used in the study are new products to be commercialized.

## **5.2. Risks and benefits**

In general, it is not expected that there will be any side effects from the use of any of the products under test, considering that they are products in routine use and commercially available. However, there is the possibility of soft tissue irritation or temporary tooth sensitivity with the use of these products, as with any oral hygiene product that is regularly used. When these conditions occur, it is recognized that they disappear with the suspension of use of the product. The oral tissue examination, which will be performed, is used as part of routine oral health care. There is also a risk of discomfort when answering the questionnaire questions. Participants will need to spend time traveling and participating throughout the study period, in addition to the need to purchase a mobile data package for the weekly questionnaires sent out. Because of this, patients will be compensated with the amount of R$50.00 (fifty Brazilian Reais), for each visit carried out, in order to offset the expenses inherent to their travel to the Faculty of Dentistry at Federal University of Pelotas. In addition, the purchase of the mobile data package will also be reimbursed with the amount of R$100.00 (one hundred Brazilian Reais) during the participants' last return.

No direct benefits are expected from participating in this study. The results of the study may help to find alternative methods to reduce the occurrence of flu and cold symptoms. Additionally, help ensure that the product is safe to market to the public. The research team will be responsible for dealing with adverse events arising from participation in the study.

## **5.3**. **Study documentation**

All data relevant to the assessments outlined in this protocol must be recorded on the forms provided. A code will be generated for each participant at the beginning of the study and this will be used in all other forms throughout the experimental period, with a view to guaranteeing anonymity. Upon completing the form, the investigator or assistant must sign the document to accept responsibilities for the purpose of recording data on each page of the form.

The following participant registration forms will be completed by the study researcher according to the following sequence:

**Initial visit**

● Consent form (Appendix A)

● Health Questionnaire (Appendix C)

● Initial Examination Form (Appendix E)

**CLINICAL EVALUATIONS**

● Examination of Soft and Hard Oral Tissues (Appendix D)

**Visit 2: day 30**

● Visit Form (Appendix H)

**CLINICAL EVALUATIONS**

● Examination of Soft and Hard Oral Tissues (Appendix D)

**Visit 3: Day 90**

● Visit Form (Appendix H)

● Delivery of the set of physical questionnaires answered during the study (Appendix F)

**CLINICAL EVALUATIONS**

● Examination of Soft and Hard Oral Tissues (Appendix D)

# **HANDLING THE TEST PRODUCTS**

## **6.1. Test products**

All test products will be supplied by Colgate-Palmolive and will be handled in accordance with the biosafety standards in force at Dentistry Faculty of Federal University of Pelotas.

## **Storage, handling and accountability of test products**

The test products will be stored in a safe area, with limited access and at room temperature. The investigator will be directly responsible for the accommodation of all products used or not used in the study. The examiner and assistant will remain blind to the treatment used for each participant. Records will be maintained to document the recipe and disposition of all products used in the study, provided by the investigator to the researcher.

## **Administration of the test products**

All participants will receive their assigned test products at initial consultation/inclusion. Participants will receive written instructions on how to use the products.

● Test product dosage: All treatments will be distributed by the study coordinator at the study location.

● Time and place of product dispensing: it will be carried out on the day/time of each participant's inclusion in the dental clinic.

● Storage of agents between appointments: All products will be kept in a closed clinical area.

# **CONCOMITANT THERAPY**

If any participant takes concomitant drug therapy, as a necessity for the treatment of a medical condition, then the participant's maintenance during the experimental period of the study will be evaluated and defined at the discretion of the investigator. However, it is the investigator's responsibility to disqualify the entry of any individual who, during initial assessments, is using or consuming products that may hinder the interpretation of study results. All medications used by participants, on the day of inclusion, or at any time during the study period, will be recorded on the Visit Form (Appendix H). Participants may be given medications to treat adverse effects as necessary by the investigator or the participant's physician.

# **ADVERSE EVENTS**

## **Definitions**

Adverse events (AEs) and serious adverse events (SAEs) are defined by the Good Clinical Practice Guidelines as follows:

**Adverse events:** Any unconventional medical occurrence in a patient or in clinical research participants who are receiving administration of a pharmacological agent and which does not necessarily need to have a causal relationship with the treatment. An adverse event can, therefore, be any unfavorable and unintended sign (including abnormal laboratory findings), symptoms or temporary illnesses associated with the use of medicinal products, whether or not related to the medicinal product.

AEs include any sign of deterioration in a participant's medical status after being enrolled in a study. AE can involve any organ or system that can be represented by the new occurrence or deterioration of the disease, a syndrome, a symptom, a physical sign, as well as by findings and results of instrumental examinations and laboratory tests. Any inconvenient change since the subject's inclusion, occurring after the first administration of the study test product, is considered an adverse effect. All such occurrences must be recorded and reported appropriately, whether they are related to the study medication or not.

## **Reporting and documentation of adverse events**

All adverse event forms are provided in Appendix B.

## **General procedures for all adverse events**

All complaints, symptoms or signs that meet the definitions of an adverse effect must be recorded on the Adverse Reactions Form (Appendix B), including the following:

• Description of the adverse event

• Start date of the reaction

• Resolution date

• Outcome

• Severity

• Seriousness

• Relationship to study drug (causality)

• Actions taken

Adverse events will be assessed by the research team in terms of severity, relationship with the product under study, and possible etiologies. The case report form proposes that all recorded adverse event outcomes be reported within two weeks after the end of the study. The investigator is responsible for tracking all adverse effects until resolution or until there are no longer any clinical concerns and providing this data to the funder. The investigator is also responsible for reporting all adverse events to Ethical Committee Research – Federal University of Pelotas, in accordance with the rules and procedures established by resolution 466/12.

# **NEW FINDINGS**

Participants will be informed of any new significant findings related to study products or procedures as they become known during the course of this clinical study.

Such information may affect the subject's decision to continue participation in the study.

# **SCHEDULE**

The current research project is expected to begin in July 2022. However, this project will only begin after approval by the Research Ethics Committee of the Faculty of Dentistry at Federal University of Pelotas.

| **Activity/Month**  **(after approval of Ethical Committee)** | **Month 1** | **Month 2** | **Month 3** | **Month 4** | **Month 5** | **Month 6** | **Month 7** | **Months**  **8 - 12** |
| --- | --- | --- | --- | --- | --- | --- | --- | --- |
| Literature research | **X** | **X** | **X** | **X** | **X** | **X** | **X** |  |
| Examiner training | **X** |  |  |  |  |  |  |  |
| Selection of participants and data collect | **X** | **X** | **X** | **X** | **X** |  |  |  |

| Data tabulation and analysis |  |  |  |  | **X** | **X** | **X** |  |
| --- | --- | --- | --- | --- | --- | --- | --- | --- |
| Writing of articles, preparation of the research report and submission for publication |  |  |  |  |  |  | **X** | **X** |

# **BUDGET**

This study has full funding from the Latin American Association for the Promotion of Oral Health and Dental Research – LAOHA.

| **Product** | **Unit price (R$)** | **Amount** | **Total (R$)** |
| --- | --- | --- | --- |
| Transportation costs | 50.00 | 450 | 22,500.00 |
| Cellphone internet plan reimbursement | 100.00 | 150 | 15,000.00 |
| Book – daily questionnaire | 30.00 | 150 | 4,500.00 |
| Copy of the questionnaires | 0.10 | 3,375 units | 337.50 |
| Copy of the informed consent forms | 0.10 | 400 units | 40.00 |
| Paper prints | 0.10 | 1000 units | 100.00 |
| Dentifrice (control regime) | 10.00 | 40.5kg | 4,500.00 |
| Dentifrice (test regime) | 10.00 | 40.5kg | 4,500.00 |
| Soft multi-bristle toothbrushes | 5.00 | 400 units | 2,000.00 |
| Mouthwash (CPC+Zn) | 15.00 | 450 units | 6,750.00 |
| Odontoscope, clinical forceps, millimiter periodontal probe | 70.00 | 30 units | 2,100.00 |
| Individual protective equipment (gloves, mask and hat) | - | - | 500.00 |
| Office supplies (pens, pencils, eraser), printer ink (existing printer) | - | - | 380.00 |
|  | | **Total** | **63,207.50** |

**APPENDIX B – ADVERSE REACTIONS FORM**

**Information’s about the participant:**

| Number of  Participant | Initials of  participante | Gender | Age | Weight | Ethnic group |
| --- | --- | --- | --- | --- | --- |
|  |  |  |  |  |  |

If the participant is a woman, are they pregnant? ( ) Yes No

If yes, how many months? _________

Date the adverse reaction was noticed: ______/______/________

Adverse reaction reporting date: ______/______/_________

Phase of the study where the first event occurred: ___________________________________

**Information’s about the product used:**

| Nome of the product (identification number): | |
| --- | --- |
| Data of first usage: | Date of interruption usage: |
| Dose: | Daily frequency: |
| Experimental group: | |

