Other studies have been carried out and sought to evaluate the potential of solutions used locally in the mouth/oropharynx region in the context of viral infections. In an *in vitro* study, using two commercially available toothpastes and two mouthwash solutions, it was observed that rinsing with hydrogen peroxide, or with cetylpyridinium chloride, or using toothpastes with stannous fluoride had important antiviral effects (RAMJI, CIRCELLO, WINSTON, et al., 2022).

Cetylpyridinium chloride (CPC) is a quaternary ammonium compound, with high safety and widespread use as an adjunct to oral hygiene procedures. It has good adherence by patients, and its antibacterial effect on the oral microbiota is undisputed (LANGA, MUNIZ, COSTA, et al., 2021). Furthermore, recently, the literature has demonstrated that the addition of zinc (Zn) to mouthwashes containing CPC has demonstrated superior clinical effects when compared to mouthwashes containing only CPC (RÖSING, CAVAGNI, GAIO et al., 2017) or essential oils (LANGA, CAVAGNI, MUNIZ et al., 2021). However, its antiviral potential is still little tested, but it has potential and has been recommended as a pre-operative mouthwash for dental procedures (RETAMAL-VALDES, SOARES, STEWART, et al., 2017).

Based on these potentials and the need for clinical studies, in addition to the possible effect of the topical use of oral antiseptics to reduce viral infections, this study is justified, which aims to evaluate the effect of using a CCP+Zn solution in the form gargling when flu and cold symptoms occur. The hypothesis under study is that the local presence of CCP+Zn can reduce the occurrence of flu-like symptoms when compared to the absence of these active ingredients.

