### Sample size

The sample size of 150 individuals (75 per group) was based on internal data from the sponsor of this study. It was determined that 60 individuals per group are needed for 80% power for the occurrence of flu-like symptoms. Considering the nature of the study and the demand for daily questionnaire responses, an attrition rate of 25% is assumed over the course of the study.

- - 1. Inclusion criteria

Individuals must meet all the following criteria:

1. Sign this informed consent form (ICF) (Appendix A);

2. Men or women, aged between 18 and 70;

3. Good systemic general health as determined by study investigators;

4. Availability of 90 days to participate in the study;

- - 1. Exclusion criteria

During the study, the following exclusion criteria will be considered:

1. Be participating in any other clinical study;

2. Being pregnant or breastfeeding;

3. Present a history of allergies to oral hygiene products, personal hygiene products, or their ingredients;

4. Have mouth irritation or use oral anesthetic sprays;

5. Have diabetes;

6. Be undergoing extensive dental treatment or oral surgery during the study;

7. Present immunocompromised (HIV, AIDS, immunosuppressive drug therapy);

8. Use complete dentures;

9. Have carpal tunnel syndrome or arthritis in the hands.

10. Participant who substantially fails to follow the required protocols;

11. Participant who fails to attend scheduled appointments;

12. Participant who is treated, during the study period, with medications that may interfere with the parameters being analyzed in the study;

13. Participant who is treated by a medical or dental service, and this may interfere with the parameters being analyzed in the study;

14. Participant who develops serious adverse reactions. The investigator will immediately record the information on the Adverse Reactions Form (Appendix B);

15. The participant who chooses to end their participation in the study;

16. Participant reports being pregnant during the study.

- 1. **Tests products**

Participants will be randomized into one of the following experimental regimens and will receive products as follows:

Group control:

● Colgate Maximum Cavity Protection® Toothpaste.

● Commercially available soft toothbrush.

Test Group:

● Mouthwash containing 0.075% CCP and 0.28% zinc lactate, in an alcohol-free base, commercially available in Brazil.

● Colgate Maximum Cavity Protection® Toothpaste.

● Commercially available soft toothbrush.

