### 4.4.3. Allocation of participants in each group

Participants included will be randomly allocated to one of the two study groups, via a website (randomization.org). The examining dental surgeon and his assistant will not receive information, throughout the study, regarding the allocation group of each participant. The products will be covered by a wrapper to maintain allocation concealment. The products will be distributed by a researcher not involved in the clinical evaluations, in a separate area from the examination and interview site and placed in a sealed bag to avoid the perception of any differences in the packaging and appearance of the products used between the two experimental groups. Label information will consist of a study group code, instructions for home use, and safety information including emergency contacts (Appendix G).

Participants will be numbered, as a form of identification, chronologically from 001 to 150, as they are included in the study. Participants living in the same house will be assigned to the same experimental group, that is, they will receive the same products.

At the initial visit, as a form of guidance, participants will be instructed to practice oral hygiene according to the experimental regimen designated by a member of the research team. In the case of the control regime, participants will be asked to brush their teeth for 2 minutes with toothpaste twice a day. In the test regime, in addition to brushing for two minutes with toothpaste, participants must gargle with the substance offered for 30 seconds, twice a day.

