**Relevant laboratory data:**

( ) Yes, list them ( ) None ( ) Not provided ( ) Unknown

- Laboratory test, results and dates if known: ______________________________________________________________________

Date: ______/______/_________

Signature of the examining dentist: __________________________________________

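### The Appendix B form can disclose the arm to an examiner the plan keeps blind, and the no-rinse control with self-scored symptoms limits any conclusion to the gargling regimen

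*Combined protocol and SAP*

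**What the plan says.** **Examiner masking.** Section 4.4.3: "The examining dental surgeon and his assistant will not receive information, throughout the study, regarding the allocation group of each participant". Section 6.2 repeats it: "The examiner and assistant will remain blind to the treatment used for each participant".

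**Adverse reactions form (Appendix B).** The product box has a field "Experimental group", next to product name (with room for an identification number), dose and daily frequency. The form also records severity and relationship to the product, and ends with "Signature of the examining dentist". Sections 4.2.3 and 4.5 have the investigator record serious reactions on it. Section 8.3 gives the assessment of severity and causality to the research team.

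**Visit form (Appendix H).** The examining dentist also signs this form. Question 6 asks whether the answers on reactions, treatment, medication or pregnancy justify leaving the participant's data out of the statistical analysis.

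**Products.** Controls get a toothbrush and toothpaste. The test group also gets a mouthwash, with a gargling instruction on its label (4.4.4, Appendix G). Section 4.4.3 describes wrappers and a sealed bag, the bag being meant "to avoid the perception of any differences in the packaging and appearance of the products used between the two experimental groups".

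**Outcome and hypotheses.** The primary outcome is the proportion of days free of all ten symptoms (4.7), which participants rate themselves each day (Appendix F). The Introduction's hypothesis is that "the local presence of CCP+Zn can reduce the occurrence of flu-like symptoms when compared to the absence of these active ingredients". Section 2 compares CPC+Zn gargling with no gargling, and section 3 compares the product with the control regimen.

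**The concern.** Two separate matters are involved.

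The first is an internal contradiction. A form that the blinded examiner signs has a place for the allocation. If it is filled in as printed, masking is lost for exactly those participants who had a reaction. The examiner then repeats their tissue exams and signs the form asking whether their data should be excluded. Section 4.7 defines no analysis set that would constrain that judgement.

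The second is a limit on interpretation. Participants know whether they were given a rinse, and they score the primary outcome. One rating of 1 on a 0 to 7 scale for any of ten symptoms, tiredness among them, ends a symptom-free day, so the outcome is sensitive to how readily people report. There is no vehicle or water gargle. A difference between the arms could therefore come from CPC+Zn, from gargling itself or from expectation, and the design cannot separate them.

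**Working it through.** **Step 1: masking, text against text.**
- Promise: the examiner and assistant never learn the group (4.4.3, 6.2).
- Form: it has fields for group and dose and is signed by the examining dentist (Appendix B).
- Reconciling text: none. No passage says these fields stay blank, take a code, or are completed by someone else.
- Which fields reveal the arm: group does, unless coded. Dose can, because only the mouthwash has a stated volume (20 ml). Product name does, unless the identification number is used. Daily frequency does not, because brushing and gargling are both twice daily (4.4.4).
- Other possible leaks: the fields on action taken with the product (including the free text on reduced use), on response to stopping or reducing it, and on reappearance after reintroduction.
- Reach: participants with an Appendix B form, from the time it is completed. Diary scoring is not reached.

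**Step 2: hypothesis against design.** The Introduction needs a comparison of the active ingredients present and absent, with all else equal. The arms also differ in gargling and in the participant's knowledge of treatment. Sections 2 and 3 ask only for a comparison of regimens, which the two arms do provide.

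**Step 3: scale of a reporting shift (illustration).** The point does not rest on a figure in the plan. The 60 per group for 80% power (4.2.1) cannot be reproduced, because no effect size, rate or SD is given. Assumptions: two-sided 0.05, and each participant's proportion of symptom-free days compared as a mean.
- Detectable difference with 60 per group: (1.960 + 0.842) × √(2/60) = 0.511 SD.
- Assumed shift: 3 days in 90 = 3.3 percentage points.

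| Assumed SD | Detectable difference (points) | Shift as a share of it | Shift in SD units |
|---|---|---|---|
| 0.10 | 5.1 | 65% | 0.33 |
| 0.20 | 10.2 | 33% | 0.17 |
| 0.30 | 15.3 | 22% | 0.11 |

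- With no true effect and a reporting shift of b SD, the two-sided rejection rate is 1 − Φ(1.96 − b/√(2/60)) + Φ(−1.96 − b/√(2/60)). For b = 0.1, 0.2 and 0.3 this gives 8.5%, 19.5% and 37.6%, instead of 5%.

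**The case against.** **The form may already be coded.** The product field invites an identification number, and labels carry a study group code (4.4.3), so a code may have been intended in the group field too. This is plausible, and it is why the finding is that the examiner can learn the arm, not that the examiner will. But no text requires a code, and the dose field remains. A group-level code in a two-arm trial also protects little: once one participant's code is linked to the rinse, everyone with that code is revealed.

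**The examiner may not grade causality.** A reader might infer from the signature that the examining dentist grades severity and causality unblinded. The documents do not support that: 8.3 names the research team, and 4.2.3 and 4.5 name the investigator as recorder. The signature shows only that the dentist sees the completed form.

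**Participant blinding is never promised.** A reader might infer from the wrappers and sealed bag a masking promise to participants that is broken. Section 4.1 does not describe the trial as blinded. The packaging sentences sit with dispensing by a separate researcher away from the examination area, so they can be read as protecting the examiner. This objection stands. What remains is that the plan never says participants are unblinded, and the packaging sentence is loosely worded.

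**The formal hypothesis already matches the design.** This also stands: the ingredient contrast appears only in the Introduction.

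**The wording changes remove no bias.** Correct. They limit what may be concluded.

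**Conclusion.** The contradiction between 4.4.3 and 6.2 on one side and Appendix B on the other is real and needs reconciling. It concerns the tissue exams, the Appendix H question 6 judgement and, where the examiner takes part, the causality ratings. It could reach the primary result only indirectly, through exclusions. The number of participants affected cannot be derived. A reader might infer that the whole test arm of 75 could be unmasked. Section 8.1 defines adverse events broadly, but 5.2 in general expects no side effects and no rate is given, so that figure has no basis.

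On interpretation, it would go too far to say that the trial cannot answer its hypothesis. It can estimate the regimen contrast of sections 2 and 3, subject to reporting bias from unblinded self-scoring. It cannot isolate CPC+Zn as the Introduction's sentence requires. A reader might also expect a positive result to be reported as an ingredient effect, but no passage says so. The remedy is a stated limit.

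The size of any bias is unknown. Both the 3 days and the SDs are assumptions, and the share of 65% to 22% shows scale only. Appendix A (the consent form) was not available, so what participants are told about masking could not be checked.

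**What to change.** 1. **Appendix B.** Remove experimental group, dose and any uncoded product name from the page the examiner sees. Have the dispensing researcher (4.4.3) record them on a separate page, attached after severity and causality are graded. Check the fields on action taken, stopping and reintroduction for the same leak. The information stays on file; only who sees it, and when, changes.
2. **Sections 4.1 and 4.4.3.** State: examiner-blinded, participants not blinded. Make clear that the wrapper and sealed bag protect the examiner's masking.
3. **Introduction.** Reword the hypothesis to the regimen contrast already in sections 2 and 3.
4. **Section 4.7.** State that a positive result will be attributed to the gargling regimen under open-label self-report, not to CPC+Zn as such.

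Cost: one form edit and a few sentences, with no new product, staff or visit. The permitted claim becomes narrower.
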